#### Phase III specificities.

A previous study with older people [19] showed that all participants struggled with internal conflicts in the process of forgiveness. An example narrative is: “To me, forgiving means forgetting and never dwelling on it again [...] when I forgive, I don’t forget, because the memory resurfaces, along with the hurt and sorrow.” These conflicts are characterized by a persistent divergence between two dimensions (or voices) of the self that do not communicate with each other [18]. This marker—self-conflict or negative self-treatment—can be addressed in therapy through the two-chair dialogue task, aiming for a satisfactory negotiation or understanding between the conflicting parts [7,43,45].

Another difficulty we anticipate is avoidance by suppression of the painful experience [18]. Consider the following example: “If I am shocked, it passes. I don’t think, I forget, I focus on other things. There is so much to live for [...] I can keep control.” This may reflect an automatic tendency to deny or avoid the emotional injury caused by the offense, hindering recognition of the interruption process and access to the repressed internal experience. We identify this marker as a potential process of self-interruption, often involving immersion in painful memories and a focus on other dimensions or problems [18,19]. The two-chair enactment task can be beneficial in bringing the automatically interrupted voice into action [43,44].

Another challenge we foresee is that older individuals might delegate the responsibility of forgiveness to others, including a divine entity [18]. For example: “Thinking about God helps, because it gives me peace, relieves me [...] The one who forgives is God.” In line with what has been observed in our studies [18,19], this response may indicate a collapse of the self in reaction to profound despair caused by the emotional injury [20,46]. This type of despair can be characterized by a sense of loss of agency, where one feels entirely powerless and submits to another (e.g., delegating forgiveness, justice or repair to a divine entity), demonstrating profound demobilization [18]. Considering this marker, tasks such as empathic affirmation [41] and compassionate self-soothing [47] can be beneficial.

#### Phase IV and Phase V specificities.

Based on our prior research [18,19], it is important to emphasize that certain emotional experiences resulting from therapy can indicate if the therapeutic process is progressing positively. These encompass physiological indicators like serenity, tranquility, and calmness; cognitive shifts such as reduced rumination, enhanced learning, and decreased negative thoughts; emotional transformation including peace, joy, and relief; behavioral adaptations towards oneself, others, and the environment; and self-transformation, characterized by satisfaction, the cultivation of new internal narratives, heightened empathy and compassion, and receptiveness to transcendence [5,13,18,19].

We anticipate that transforming the emotional difficulties associated with emotional injury and fostering self-narrative reconstruction may pose a significant challenge for this population. This age group is particularly susceptible to promoting satisfactory personal integration and enhancing positive life meaning, which are crucial developmental tasks at this stage of life [48]. Indeed, we see this as a consolidation of change, a reconciliation of the self with one’s life, necessitating specific narrative-meaning reconstruction work, as outlined in the self-narrative reconstruction task [19,20], which we consider particularly suitable for this population [6,13].

### Therapists

Sessions will be administered by psychologists with several years of psychotherapy training research and clinical practice in EFT. The first author–[name]–holds a PhD in Theology and a PhD in Psychology (specialization in Clinical Psychology), and is a psychologist with previous training in EFT [18,19,49]. The second author–[name]–is a psychologist with a PhD in Psychology (specialization in Clinical Psychology). She is a specialist in Clinical and Health Psychology, holding an advanced specialization in psychotherapy, as recognized by the National Psychologists’ Association. Furthermore, she is a certified EFT therapist and supervisor, as accredited by the International Society of Emotion-Focused Therapy (isEFT). She provides supervision and training in EFT and will serve as one of the ongoing supervisors for the team. Additionally, she has authored several scientific articles in the field [18–20].

Our therapy team will also involve two more psychologists with training in EFT, involved in the PhD program of the university. All therapists will be trained in this protocol [2] and supervised by a certified EFT supervisor. The therapists, with a commitment to avoiding any form of ageism, will be encouraged—through peer supervision—to address the key vulnerabilities, needs, and potential of this client population age group [6,15]. In addition to the four psychologists who are part of the therapy team, this research will involve another psychologist who will be responsible for the recruitment process and the assessment procedures. This psychologist—to safeguard the reliability of the evaluation results—will not be involved in the therapeutic process.

### Therapy fidelity

The team of therapists will be provided with and instructed on a therapy protocol. They will also receive a checklist outlining specific procedures typical of each therapy phase. Therapy sessions will be audio and video recorded, and a selection of these recordings will be randomly analyzed by psychologists with supervisory experience in EFT to ensure adherence to the model and fidelity of therapy procedures. Therapists will receive supervision from a qualified EFT supervisor, which will involve corrective feedback to ensure therapist adherence and competence in relation to the EFT model [20,41]. To evaluate how closely therapists follow the EFT model, we will use the Person-Centered and Experiential Psychotherapy Scale (PCEPS-EFT-9) [50]. This scale evaluates treatment integrity in EFT, namely a qualitative assessment of the adherence to protocol and competence level for each EFT therapist, based on their observable performance (using a Likert scale from one to six in nine distinct competencies).

### Participant retention

To minimize possible abandonment of therapy, those involved in the study will always be alerted in advance about their appointments and will have the possibility of rescheduling them if clients are unable to attend [22,29].

### Assessments and measures

Several questionnaires will be used to assess the acceptability, feasibility, and to explore the outcomes of the therapy—see Figs 1 and 2.

#### Intervention acceptability measures.

*Therapy Credibility and Expectancy*

We will use the Credibility/Expectancy Questionnaire (CEQ) [51,52] to measure treatment credibility and client outcome expectations. The CEQ is a self-report questionnaire composed of six items grouped into two subscales: treatment credibility and expected outcome–on a 9 item Likert scale. Credibility assesses the degree of confidence that participants have in the usefulness of therapy as treatment for their difficulties. Client outcome expectations assesses how much participants believe they can benefit from the therapy protocol that is provided [52].

*Session Satisfaction Module*

To evaluate participants’ assessment of each specific session of the intervention protocol, they will be asked at the end of each session to rate how beneficial they found each session and corresponding homework activity. This will be done through a simple question, with responses varying on a 5-point Likert scale [22].

*Global Therapy Satisfaction*

To assess participants’ satisfaction with the global intervention, we will use the Client Change Interview Protocol (CCIP) [40,53]. This semi-structured interview, comprising open-ended questions, has a duration of approximately 60 minutes and is administered at the conclusion of therapy (at t3 and t5). The CCIP explores potential processes of change experienced by clients during therapy, covering attributions, meanings, and relevance. Participants evaluate specific changes they have experienced using a 5-point scale, assessing the extent to which these changes were expected, likely without therapy, and their perceived value [54]. Any negative evaluations derived from the Session Satisfaction Module will also be examined. Consequently, these procedures are intended to facilitate necessary adjustments to the treatment protocol, thereby enhancing its feasibility and acceptability based upon client feedback.

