### Therapy

Participants will be offered twelve in-person sessions, scheduled once a week. The therapy is structured into five phases (Table 2), following the protocol proposed by Meneses and Greenberg (2019). This approach emphasizes emotions in the therapeutic process and addresses the primary difficulties reported by adults in relation to forgiveness. Each session will be adapted to meet the specific needs of the clients.

**Table 2 pone.0345792.t002:** EFT for the resolution of emotional injuries session: An overview.

Phase	Content	Home Practice
Phase I:	Creating an alliance	Diary of feelings towards the injurer.
Phase II:	Evocation and exploration	Particular attention can be given to awareness of emotional experiences
Phase III:	Self-interruption work Empty-chair work	Drafting the letter to the injurer and its response (for personal use only); encouraging reflection and the identification of difficulties in forgiveness
Phase IV:	Empowerment and letting go or forgiving	Narratives of new meanings of the experience and the injurer
Phase V:	Termination	

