#### Intervention feasibility measures.

*Recruitment rates*

Refers to the number of participants able to join the therapy as a result of the recruitment process.

*Participation rates*

Participants who completely discontinue therapy should be classified as dropouts.

*Questionnaire feasibility*

The feasibility of the questionnaires will be measured by evaluating the completion rates of the questionnaires including client feedback and the degree of missing data.

*Homework evaluation*

To assess the value of homework, an adapted version of the Homework Rating Scale (HRS) [55] will be employed, consisting of seven questions rated on a 5-point Likert scale. Participants will be asked to evaluate their level of achievement, understanding, effort, utility, relevance, satisfaction, and the impact of the exploratory tasks assigned during the therapy weeks [22].

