### Data collection

As illustrated (Fig 2), various measures will be administered throughout the study—from participant selection to the two planned follow-up assessments. To minimize the burden on participants, questionnaires scheduled for completion at the end of the therapy will be distributed either during the final session or at home between sessions. The questionnaires will be returned in sealed envelopes to the therapists, who will then hand them over to the psychologist responsible for the evaluation process. This independent psychologist will also conduct the initial assessment for study integration and the final qualitative interview [22,29].

To efficiently assess whether potential participants meet the study criteria, eligible individuals will undergo the Structured Clinical Interview for DSM-5—Research Version (SCID-5-RV) [59] and the Montreal Cognitive Assessment (MoCA) [37,38]. Additionally, socio-demographic data, including age, gender, occupation, religious beliefs, current medications, and details regarding the interpersonal offense or emotional injury experienced, will be collected at the outset [22,25,34].

After participants are assigned to their respective groups, three assessment points will be established: before therapy begins, at the sixth session, and at the final session. These assessments will focus on Forgiveness, Letting Go, Quality of Life, and Depression. Before therapy commences, the CEQ will also be administered. Following each session, the Satisfaction Therapy Module and Homework Evaluation will be conducted. Upon completion of therapy (t3 and t5), the CCIP will be administered. To ensure adherence to the therapy protocol, sessions will be recorded for subsequent supervisory evaluation [22,29,34]. Research assistants will provide updates and reminders for follow-ups via telephone and/or email.

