### Progression criteria

This study protocol will be developed for broader research based on the assessment of its acceptability and feasibility. Regarding the CEQ measure, the study will proceed without changes if the result is ≥ 6 on a 9-point Likert scale. The study will also progress without changes in the Session Satisfaction Module if the result is ≥ 3 on a 5-point Likert scale [22]. For recruitment, the progression criterion will be a rate of 75–100% of the sample size [61]. The criterion for retention level will be a rate >80% [36]. The progression criterion for the questionnaires will be a response rate >90%. For homework assessment, a score of ≥ 3 on a 5-point Likert scale will be required [22,29].

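### One Session Satisfaction question rates both the session and its homework, so the ≥3 session criterion mixes the two; the separate homework scale does not say which homework it covers

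*Protocol article*

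**What the plan says.** The section on intervention acceptability measures describes the Session Satisfaction Module. Participants are asked "at the end of each session to rate how beneficial they found each session and corresponding homework activity". The format follows: "This will be done through a simple question, with responses varying on a 5-point Likert scale".

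The section on intervention feasibility measures gives homework its own instrument, an adapted Homework Rating Scale "consisting of seven questions rated on a 5-point Likert scale". Participants are to "evaluate their level of achievement, understanding, effort, utility, relevance, satisfaction, and the impact of the exploratory tasks assigned during the therapy weeks".

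The Data collection section times both instruments together: "Following each session, the Satisfaction Therapy Module and Homework Evaluation will be conducted".

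Table 2, in the Therapy section, lists home practice by phase rather than by session. The Phase I entry, for example, is "Diary of feelings towards the injurer". The cell for Phase V (termination) is empty.

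The Progression criteria section sets six criteria: credibility/expectancy, session satisfaction, recruitment, retention, questionnaire response and homework. Session satisfaction must reach at least 3 on a 5-point scale. The homework criterion is separate: "For homework assessment, a score of ≥ 3 on a 5-point Likert scale will be required".

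**The concern.** A question that asks for one answer about two objects is double-barrelled: the answer cannot be assigned to either object. Here the objects are the session and the homework attached to it. The module is introduced as the way participants evaluate each specific session, and its result is one of the conditions for going forward without changes. If the answer also carries the participant's view of the homework, the criterion does not measure what it is meant to measure.

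The second issue is timing. Both forms are given after every session, and nothing says which homework a form refers to. Several of the homework items make sense only once a task has been done.

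At stake is the use the protocol makes of these ratings, which is to decide what to adjust before a larger trial. Error rates and sample size are not involved, because these measures are summarised descriptively.

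**Working it through.** The plan gives no figure to reproduce. The check sets the relevant sections side by side.

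**Step 1: what the session criterion rests on.** The inputs are one question, one 5-point answer and two named objects (acceptability measures), with a threshold of ≥3 (Progression criteria). For illustration only, assume that a participant gives the two parts equal weight, so that the answer is (session + homework) / 2:

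| View of session | View of homework | Combined answer | Meets ≥3? |
|---|---|---|---|
| 5 | 1 | (5 + 1)/2 = 3 | yes |
| 1 | 5 | (1 + 5)/2 = 3 | yes |
| 3 | 3 | (3 + 3)/2 = 3 | yes |

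Three different situations give the same answer and the same decision. The ratings and the equal weighting are assumptions; the protocol states neither.

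**Step 2: whether another measure separates them.**
- *Homework side: yes.* The Homework Rating Scale covers homework alone and has its own ≥3 criterion. In the first row, the low view of homework should appear there.
- *Session side: no.* The credibility/expectancy questionnaire is given before therapy starts. The change interview comes at the end of therapy (t3 and t5), and its scaled ratings concern changes the participant experienced, not single sessions. The fidelity scale is scored by supervisors from recordings. In the second row, both criteria can be met although the session was rated at the bottom of the scale.

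The gap is therefore one-sided. Poorly received homework has a second check; a poorly received session does not.

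**Step 3: which homework the homework scale covers.** The form is given after each session, and there are two readings.
- *The homework just set.* It has not been done when the form is completed, so achievement, effort and impact cannot be rated. Where Table 2 lists no home practice (Phase V), there is nothing to rate at all.
- *The homework done since the previous session.* The items can be answered, but session 1 has no earlier homework.

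Neither reading fits all twelve sessions. The instrument's own description, "the impact of the exploratory tasks assigned during the therapy weeks", does not settle which week is meant.

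**The case against.** The case for leaving the text alone has several parts.

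- **Homework is already protected.** A reader might infer that disliked homework can hide behind well-liked sessions and let the study progress unchanged. The documents do not support that: the separate scale covers utility, relevance, satisfaction and impact, and must itself reach ≥3. This objection stands, and it limits the double-barrelled problem to the session criterion.
- **Homework may not be rated in the session that sets it.** A reader might infer that it is, and that the ratings therefore capture anticipation only. No section says so. The achievement and effort items presuppose completed tasks, the satisfaction question is put in the past tense, and a task listed for a whole phase could be under way by a later session. This also stands. What remains is that the reference period is unstated.
- **Other sources of feedback exist.** Negative satisfaction ratings are to be examined, and there is an interview of about 60 minutes. This helps in part. A mid-scale combined answer of 3 meets the criterion and need not be picked out as negative, and an end-of-therapy interview is a weak guide to particular sessions.
- **The article is condensed.** Exact item wording may sit in forms that are not shown, and the figures that show the schedule are missing here. The forms might clarify matters. But the article does state that there is one question, what it covers, when it is asked and what threshold applies, and the point concerns those statements.

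**Conclusion.** The point holds in limited form and is minor. As printed, the session-satisfaction criterion, one of six, rests on a rating that mixes session and homework, and no other numeric participant rating isolates the session. The homework criterion does not share this fault. It is affected only because the homework being rated is not identified, which leaves at least session 1 or Phase V without an object, depending on the reading.

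Two stronger conclusions are not supported. A reader might infer that both ratings are uninterpretable. The combined item still gives a crude overall benefit score, and the homework scale can be interpreted if it refers to completed tasks. A reader might also infer that forms with nothing to rate would push questionnaire response below its >90% criterion. The documents do not say that such forms count as missing, how the forms are pooled, or how many sessions Phase V takes, so no such shortfall can be derived.

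The conclusion assumes that the module is administered as described, with one answer for both parts. If the actual form has two separate items, the first part falls away and the article's wording needs only correction.

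**What to change.** 1. Reword the Session Satisfaction item so that it rates the session only, keep it at session end, and apply the ≥3 session criterion to that item. Drop homework from it, since the Homework Rating Scale already covers homework.
2. State that the Homework Rating Scale refers to homework done since the last session. Give it from session 2 on, and only where homework was set.
3. Leave forms that do not apply out of the expected count when questionnaire completion is calculated.

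The cost is one reworded item and a short statement of reference period in the Data collection section, with no additional item, visit or staff. The downside is about a week's recall for homework ratings. According to the Recruitment section, enrolment has not started and is planned for 2026, so the change can be made before any data are collected.

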## Abstract

Over recent decades, Emotion-Focused Therapy, aging, and forgiveness have garnered significant attention in the field of psychology. However, there is a lack of studies on Emotion-Focused Therapy and forgiveness specifically tailored for older adults. This article presents a protocol designed to assess the feasibility and acceptability of a randomized controlled trial of Emotion-Focused Therapy aimed at resolving emotional injuries in individuals aged 65 and older, within the context of interpersonal offenses. Feasibility will be evaluated through recruitment and retention rates, as well as adherence to the intervention protocol. Acceptability will be assessed based on perceived treatment credibility, participants’ expectations regarding outcomes, levels of engagement, and overall satisfaction with the intervention. The study is structured as a two-arm, parallel-group randomized trial with a waiting list control. We propose recruiting a sample of 70 participants, randomly assigned to either an immediate intervention group, which will receive Emotion-Focused Therapy over twelve weekly sessions, or a control group that will receive the same therapy after a twelve-week waiting period. Data will be collected in the beginning, middle, and at the end of therapy, and in two planned follow-ups (three and six months after therapy). Once this protocol is implemented, if the therapy proves to be feasible, acceptable, and shows promising results, the findings will inform a large-scale randomized clinical trial to advance the understanding of this treatment for individuals aged 65 + .

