#### Primary objectives.

a. To assess the feasibility of the therapy and assessment protocol using key evaluation indicators, including recruitment rate, retention rate, and engagement rate.b. To evaluate the acceptability of the therapy, considering the following indicators: treatment credibility and client outcome expectations, engagement, and satisfaction.

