#### Qualitative analysis.

The data collected from the CCIP will be recorded. After being transcribed, it will be subject to respective analysis.

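### Overall satisfaction, a primary acceptability indicator, is assigned to an interview described as being about change; the protocol describes no direct rating of satisfaction with the whole therapy and no progression criterion for it.

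*Protocol article*

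**What the plan says.** The abstract lists, among the things on which acceptability will be judged, "levels of engagement, and overall satisfaction with the intervention". Under Primary objectives, item b gives the indicators of acceptability as "treatment credibility and client outcome expectations, engagement, and satisfaction".

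Under Intervention acceptability measures, the paragraph on Global Therapy Satisfaction names the instrument: to assess "satisfaction with the global intervention, we will use the Client Change Interview Protocol (CCIP"). It then describes the instrument in three steps:

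- Format: "This semi-structured interview, comprising open-ended questions, has a duration of approximately 60 minutes", given at t3 and t5.
- Content: "The CCIP explores potential processes of change experienced by clients during therapy, covering attributions, meanings, and relevance".
- Ratings: participants rate specific changes on a 5-point scale, "assessing the extent to which these changes were expected, likely without therapy, and their perceived value".

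The same section has a Session Satisfaction Module, in which participants are asked "to rate how beneficial they found each session and corresponding homework activity". The quantitative analysis section lists the CCIP among the acceptability and feasibility measures to be explored descriptively. The qualitative analysis section says of the interview data: "After being transcribed, it will be subject to respective analysis". The Progression criteria section has a threshold for the session rating but does not mention the CCIP or global satisfaction.

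**The concern.** The label and the described content do not match. The label is satisfaction with the whole therapy. The content is change: what changed, why, and what it meant. These are different quantities. A participant may value a change and still be dissatisfied with how the therapy was delivered. Another may be satisfied with the therapy and report little change, and so have few changes to rate.

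This matters because the abstract treats acceptability and promising results as separate conditions for going on to a larger trial. If the evidence on overall satisfaction comes mainly from talk and ratings about change, the acceptability finding can drift towards a second report of perceived outcome. The reader of the results could not then tell the two apart for this indicator.

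**Working it through.** No arithmetic applies beyond counting. The check is to list every instrument the protocol describes that could carry a satisfaction rating, and to ask whether it rates satisfaction with the therapy as a whole and whether it has a progression criterion.

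| Instrument | What is rated, as described | When | Rates satisfaction with the whole therapy? | Progression criterion |
|---|---|---|---|---|
| CEQ | Credibility and expected outcome | Before therapy | No; it precedes the therapy | ≥ 6 of 9 |
| Session Satisfaction Module | Benefit of the session and its homework, one question, 5 points | After each session | No; one session at a time, and worded as benefit | ≥ 3 of 5 |
| Homework Rating Scale (adapted) | Seven 5-point questions on homework, one on satisfaction | After each session | No; satisfaction with homework tasks | ≥ 3 of 5 |
| CCIP ratings | Each change: expected, likely without therapy, valued | t3 and t5 | No; all three are attributes of a change | None |
| CCIP open-ended questions | Processes of change; guide not printed | t3 and t5 | Possible, but not described | None |

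Counts from the table and the Progression criteria section:

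- Rating dimensions described for the CCIP: 3. Those that rate satisfaction with the therapy: 0.
- Direct ratings of whole-therapy satisfaction described anywhere in the protocol: 0.
- Progression criteria: 6 (CEQ, session rating, recruitment, retention, questionnaire response, homework). Those for overall satisfaction: 0.

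The analysis sections do not close the gap. The quantitative section names the CCIP but no satisfaction score. The qualitative section does not say how satisfaction would be drawn from the transcripts. What remains for overall satisfaction is whatever the open-ended part of the interview brings out.

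**The case against.** The strongest reply is that the three ratings are only one part of a 60-minute, mainly open-ended interview, and that an end-of-therapy interview is an ordinary way to learn about satisfaction in a descriptive feasibility study. The interview guide is not printed, and an article commonly leaves it to the full protocol, so a satisfaction question cannot be ruled out. Neither the abstract nor the objective promises a number. The CCIP does not stand alone either: negative session evaluations will also be examined, the session rating is repeated and has a threshold, and the homework scale contains a satisfaction question.

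All of this stands, and it limits the point. A reader might infer that the trial yields no measure of satisfaction at all. The documents do not support that, because the open-ended questions may elicit it and related ratings exist at session and homework level. A reader might also infer that the change ratings will be scored and reported as satisfaction. No section says so; mixing the two is a risk, not a stated plan.

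The reply does not remove the mismatch in the printed text. The paragraph headed Global Therapy Satisfaction describes an instrument about change. The session and homework ratings concern parts of the therapy, and the session question asks about benefit.

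**Conclusion.** The point holds in a limited form. As described, overall satisfaction is assigned to an interview about change, with no direct rating of satisfaction with the whole therapy and no progression criterion. One named indicator within a primary objective is affected; the other acceptability and feasibility measures are untouched, and no stated figure is in error. A qualitative indicator without a threshold is legitimate in itself, so this is a cheap improvement and not the correction of a mistake that would invalidate the trial.

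The conclusion assumes that the article's description of the CCIP is representative of the interview to be used. If the unprinted guide contains a question on overall satisfaction, and a way of coding the answers, what remains is mainly to say so in the text and to decide whether the indicator should enter the progression decision.

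**What to change.** Add one 5-point item on satisfaction with the therapy as a whole, completed with the end-of-therapy questionnaires at t3. Report its mean and distribution as the overall-satisfaction result. List it under Progression criteria on the same basis as the session rating, which requires at least 3 of 5. Keep the CCIP, described as the complementary qualitative measure of perceived change and client feedback, so that satisfaction and perceived outcome are reported separately.

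If the sponsor prefers no new item, the lesser alternative is to state which CCIP questions address satisfaction and how the answers will be coded. That clarifies the plan but still gives no direct rating.

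The cost is one extra question per participant at an existing contact, one more progression criterion, and small wording changes in the acceptability measures and progression sections. The protocol states that recruitment has not started, so the change can be made before any data are collected.
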